## **5. OBJECTIVES AND ENDPOINTS**

### **5.1 Primary objective**

The primary objective of this study is to evaluate the efficacy of a single 25 mg oral dose of psilocybin for recurrent major depressive disorder (MDD) compared to an active placebo (niacin) in otherwise medically-healthy participants ages 20 to 65, assessed as the difference between groups in changes in depressive symptoms.

#### **5.1.1 Primary study endpoint**

Between-group difference in change of blinded rater Montgomery-Asberg Depression Rating Scale (MADRS) total score from Baseline to post-dose Day 8.

##### **5.1.1.1 Justification for primary study endpoint**

As with other rapidly acting investigational antidepressant agents (e.g. ketamine), a single dose of psilocybin has shown to induce a large effect-size reduction in depressive symptoms within a day of administration in comparison to active placebo, with no further improvement in symptom scores seen at subsequent assessment points (i.e. at 2 weeks and 6 weeks post-intervention). These findings demonstrate that an assessment at one week post-intervention will likely capture the entire antidepressant effect of psilocybin, both in comparison to active placebo and in comparison to baseline symptom score. Further support for the appropriateness of one week post-intervention as the primary study endpoint comes from the association of immediate (e.g. one day post-intervention) and longer-term (e.g. six weeks post-intervention) antidepressant responses to both psilocybin and niacin in the New York University (NYU) study of depressed/anxious patients with cancer. In that study reductions in Beck Depression Inventory (BDI) and Hospital Anxiety and Depression Scale (HADS)

depression subscale scores between baseline and one day post-intervention were similar to reductions in BDI and HADS depressive subscale scores between baseline and six weeks post-intervention (*unpublished data*), as shown in this table:

| Instrument      | Niacin                     | Psilocybin                    |
|-----------------|----------------------------|-------------------------------|
| HADS-Depression | .750 ( $p = .002$ ) | .925 ( $p = .000016$ ) |
| BDI             | .863 ( $p = .001$ ) | .877 ( $p = .000082$ ) |

These results indicate that the impact of psilocybin on depressive symptoms at one-week post- intervention is likely to be a near perfect proxy for its longer-term effects, which further strengthens its appropriateness as a primary study endpoint in the proposed study. Because this study proposes the impact of psilocybin vs. active placebo on MADRS score at Day 42 post-dose as a secondary endpoint, results from the NYU study strongly suggest that this endpoint will be met, if indeed the primary endpoint is confirmed.

The selection of the MADRS to assess the study's primary endpoint is consistent with it being the most commonly used assessment tool for assessment of primary endpoints in recent phase 3 antidepressant registration trials. This is consistent with data indicating that in comparison to the other historically-used instrument, the Hamilton Depression Rating Scale (HAM-D), the MADRS shows improved ability to capture meaningful clinical improvement in response to active antidepressants versus placebo.

### 5.1.2 Secondary endpoints

The following secondary endpoints will be evaluated to support the primary objective:

- Change in MADRS total score from Baseline to post-dose Day 15, 42, 180 and 365 (end of study) respectively.
- Change in MADRS total score from Baseline to the treatment period (mean of Day 8-365)
- Change in MADRS-S score from Baseline to Day 365 (end of study)
- Change in MADRS-S score from Baseline to the treatment period (mean of Day 8-365)
- Response rate at all time points post dose (MADRS and MADRS-S)
- Remission rate at all time points post dose (MADRS and MADRS-S)
- Change in Sheehan Disability Scale (SDS) score from Baseline to Day 365 (end of study)
- Change in SDS score from Baseline to the treatment period (mean of Day 8-365)
- Change in Clinical Global Impression (CGI) score from Baseline to Day 8, 42, 180 and 365 (end of study) respectively
- Change in CGI score from Baseline to the treatment period (mean of Day 8-365)
- Time to initiation of antidepressant treatment

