## 5.3 Exploratory Objectives and endpoints

The exploratory objectives of this study are to evaluate the efficacy of a single 25 mg dose of psilocybin for MDD compared to an active placebo in medically-healthy participants ages 20 to 65, measured as between-group differences in:

- Change in p11 concentration in PBMC subsets from Baseline to day 15 Post dose
- Change in BDNF and VEGF concentration in plasma from Baseline to day 15 Post dose
- Change in kynurenic acid in CSF from Baseline to day 15 Post dose
- Change in monoamine and monoamine metabolites in CSF from Baseline to day 15 Post dose
- Change in cytokine concentration (exact markers to be determined based on current literature at time of analysis) in CSF from Baseline to day 15 Post dose
- Change in metrics of whole-brain connectomics and hub characteristics of medial and ventrolateral prefrontal cortex as well as orbitofrontal cortex in the psilocybin treated group as compared to the placebo group, and in relation to clinical outcome (MADRS) as well as PET-outcome (resting state fMRI).
- Change in influence of top-down priors in an instructed fear learning paradigm and its relation to a change in activity of the ventromedial prefrontal cortex and lateral orbitofrontal cortex in the psilocybin treated group as compared to the placebo group, and in relation to clinical outcome (MADRS) as well as PET-outcome (tasked based fMRI).
- Change in Emotion detection under perceptual uncertainty and perspective-shifting ability in relation to large-scale network activity patterns in the psilocybin treated group as compared to the placebo group, and in relation to clinical outcome (MADRS) as well as PET-outcome.
- Change in anxiety symptoms from Baseline to post-dose Day 8, 15, 42 and 365
- Change in functional disability to post-dose Day 8, 15, 42 and 365
- Change in health-related meaning of life and satisfaction with life from Baseline to post-dose Day 8, 15, 42 and 365
- Change in psychological flexibility from Baseline to post-dose Day 8, 15, 42 and 365
- Correlations between biomarkers and scales

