## 5.5 Outcome Measures

### 5.5.1 Montgomery-Asberg Depression Rating Scale (MADRS)

The MADRS is a 10-item depression rating scale developed in 1979 to be more sensitive to symptom changes induced by antidepressants than were currently available instruments. The MADRS has been used for assessing primary outcomes in registration trials for new pharmacological agents for treating MDD, whether these agents are traditional monoamine modulators or agents with novel mechanisms of action (e.g., esketamine). The MADRS includes questions on the following symptoms 1) Reported sadness, 2) Apparent sadness, 3) Inner tension, 4) Reduced sleep, 5) Reduced appetite, 6) Concentration difficulties, 7) Lassitude, 8) Inability to feel, 9) Pessimistic thoughts, and 10) Suicidal thoughts. Items are scored via a clinical interview that progress from more broadly phrased questions about symptoms to more detailed queries that allow a precise rating of severity. Items are rated to capture the patient's clinical state over the prior week. Each item yields a score of 0 to 6, and higher scores indicate more severe depression. The overall score ranges from 0 to 60.

Various studies have suggested cut scores from  $< 9$  to  $< 12$  as a definition of remission. For the current study, remission will be defined as a score  $\leq 10$ . Response will be defined as  $\geq 50\%$  decrease compared to the last measurement before dosing.

MADRS-S is the self-rating version of MADRS. Apart from item 1 in MADRS, that is deleted from MADRS-S, the two scales are identical.

To reduce the risk of functional unblinding during collection of the primary study outcome measure, MADRS assessments will be conducted by a blinded rater. Raters will be blinded to participant allocation. At any occasion, if a face to face interview is not possible, a non-recorded video interview via an encrypted link will take place.

MADRS ratings will be performed at screening, PET1, day 0, 8, 15, 42, 180 and 365.

At day of dosing, results of MADRS (item 2-10) and MADRS-S before dosing will be used for validation purposes.

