#### **5.5.4 Clinical Global Impression – Improvement and Severity (CGI-I and CGI-S)**

The CGI rating scales are measures of symptom severity, intervention response and the efficacy of interventions in intervention studies of patients with mental disorders. The CGI-S is a 7-point scale that requires the rater to rate the severity of the patient's illness at the time of assessment, relative to the clinician's past experience with patients who have the same diagnosis. Possible ratings are:

1. Normal, not at all ill
2. Borderline mentally ill
3. Mildly ill
4. Moderately ill
5. Markedly ill
6. Severely ill
7. Among the most extremely ill patients

CGI-I is a 7-point scale that requires the rater to rate the change of the patient's illness compared to the baseline (ie first) assessment regardless of cause. Possible ratings are:

0. Not assessed
1. Very much improved
2. Much improved
3. Minimally improved
4. No change
5. Minimally worsened
6. Much worsened
7. Very much worsened

CGI- S and CGI-I will be collected at the same time points (day 0 (only CGI-S), 8, 15, 42, 365), by the same rater, as MADRS, and the results will be documented by the interviewer in the eCRF at time of interview.

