| CGI-S                      | 1             |     |                |                 |                 |           |    |       | MD1            |       |             | MD1      | MD2                |
| CGI-I                      | 1             |     |                |                 |                 |           |    |       |                |       |             | MD1      | MD2                |
| T-Eval (SRP)               | 1             |     |                |                 |                 |           |    |       |                | MD_M  |             |          | MHS_N              |
| Total duration/day (min)   |               | 13  | 145            | 61              | 60              | 146       | 74 | 480   | 157            | 3     | 90          | 277      |                    |
| Visit at research site (v) |               |     | v              | v               | v               | v         | v  | v     | v              | v     | v           | v        | v                  |

Time schedule: Day 43-365

| Activity                   | Dur. (min) | 42(±3) | 72(±5) | 102 (±5) | 132 (±5) | 162 (±5) | 192(±5) | 223 (±5) | 253 (±5) | 283 (±5) | 313 (±5) | 343 (±5) | 365 (±14) |
|----------------------------|------------|--------|--------|----------|----------|----------|---------|----------|----------|----------|----------|----------|-----------|
| MADRS                      | 10         | MD1    |        |          |          |          |         |          |          |          |          |          | MD1       |
| MADRS-S (SRP, TC)          | 3          | X      | X      | X        | X        | X        | X       | X        | X        | X        | X        | X        | X         |
| GAD-7 (SRP, TC)            | 1          | X      | X      | X        | X        | X        | X       | X        | X        | X        | X        | X        | X         |
| EQ-5D (SRP, TC)            | 1          | X      | X      | X        | X        | X        | X       | X        | X        | X        | X        | X        | X         |
| SDS (SRP, TC)              | 1          | X      | X      | X        | X        | X        | X       | X        | X        | X        | X        | X        | X         |
| AAQ-II & ALIVE (SRP)       | 1          | MD1    |        |          |          |          |         |          |          |          |          |          | MD1       |

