### **8.5.2 Magnetic Resonance Imaging (MRI)**

After informed consent and before Lumbar Puncture (day 7-35 before dosing), MRI1 will take place at MR-centrum Solna. The visit will take approximately 1 hour and will include structural functional sequences including a set of tasks (see 14).

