#### **15. MAGNETIC RESONANCE IMAGING (MRI) EXPERIMENTAL PROCEDURE AND DATA ACQUISITION**

Collection of MRI data will occur on two occasions: 1) as a part of post preparatory assessment (7-35 days prior to dose) and 2) day 1, post dose, i.e the day after the treatment has been given. Brain imaging sessions will be performed at the Solna MRI center, Department of Clinical Neuroscience, Karolinska Institutet. on a 3-Tesla GE scanner. The protocol includes acquisition of structural 3D T1 MPRAGE, three functional MRI (fMRI) tasks, Diffusion Tensor Imaging (DTI), resting state fMRI (rsfMRI) with presentation of abstract figures – all are standardized methods at the MRI center. The fMRI tasks will include: reversal aversive learning (RALT), perspective shifting (P-SHIFT), and emotion detection under perceptual uncertainty (EDPU). During the first session no task-based fMRI will be performed, otherwise the sessions are the same. The planned scanning session will take 1 hour (session 1) and 1.5 hours (session 2) to complete including preparations and instructions. Research coordinators and assistants possessing an MRI driver license are supervising these assessments. The MRI scanning sessions can be stopped by the subject at any time by activating a squeeze-ball provided to the subjects in order to inform the researchers that the procedure needs to be terminated.

In case of accidental finding requiring medical attention (the scans will be evaluated by a neuroradiologist) the subject will be contacted by the responsible study MD and further steps will be discussed (e.g. referral to a specialist).

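### The endpoint lists and the assessment schedule contradict each other on Day 180 rater MADRS and CGI, and on whether task fMRI is run before dosing

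*Protocol*

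**What the plan says.** **Day 180.** The synopsis, protocol section 5.1.2 and SAP section 3.2 all name two secondary endpoints with a Day 180 time point: "Change in MADRS total score from Baseline to post-dose Day 15, 42, 180 and 365 (end of study) respectively" and "Change in Clinical Global Impression (CGI) score from Baseline to Day 8, 42, 180 and 365 (end of study) respectively". The scale description in protocol section 5.5.1 agrees for MADRS: "MADRS ratings will be performed at screening, PET1, day 0, 8, 15, 42, 180 and 365". The CGI description in section 5.5.4 does not; CGI "will be collected at the same time points (day 0 (only CGI-S), 8, 15, 42, 365), by the same rater, as MADRS". The part of Table 1 headed "Time schedule: Day 43-365" marks rater MADRS, CGI-S and CGI-I at Days 42 and 365 only.

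**Task fMRI.** Section 5.3 defines exploratory endpoints as changes, for example "Change in influence of top-down priors in an instructed fear learning paradigm", with a companion endpoint for emotion detection and perspective shifting. Section 15 says of the scans: "During the first session no task-based fMRI will be performed, otherwise the sessions are the same". Section 8.5.2 says that the pre-dose scan (MRI1) "will include structural functional sequences including a set of tasks", and section 9.4.1 describes the post-dose scan as a repeat of the same sequences.

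**The concern.** An endpoint needs a planned observation behind it. Section 8 of the protocol requires adherence to the Schedule of Assessments, and section 9 sends the reader to Table 1 for timing and frequency. Table 1 is therefore what a site will work from. A site that does so makes no rater assessment at Day 180, although the endpoint lists expect two. A site that follows section 15 has no pre-dose task scan, although the endpoints are worded as changes.

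Neither kind of data can be recovered later. A blinded rating at Day 180 cannot be made in retrospect, and a pre-dose scan cannot be made after dosing. If sites or staff read different sections, the data could also be present for some patients and absent for others, for reasons unrelated to the trial's questions.

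**Working it through.** The plan gives no computed figure on this point, so the check compares the sections with one another.

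**Step 1. Does any Table 1 window after Day 15 contain Day 180?** Window = nominal day ± allowance.

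- Day 162 ±5 covers 157 to 167. Day 180 is 180 − 167 = 13 days after it closes.
- Day 192 ±5 covers 187 to 197. Day 180 is 187 − 180 = 7 days before it opens.
- The other columns (42 ±3, 72, 102, 132, 223, 253, 283, 313 and 343, each ±5, and 365 ±14) lie further away.

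No window contains Day 180. The Day 162 and Day 192 contacts carry only MADRS-S, GAD-7, EQ-5D and SDS, all self-rated.

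**Step 2. Where does each section stand on Day 180?**

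| Source | Rater MADRS | CGI |
|---|---|---|
| Synopsis endpoints, 5.1.2, SAP 3.2 | yes | yes |
| Scale description (5.5.1, 5.5.4) | yes | not in its day list |
| Table 1 | no | no |
| Synopsis visit list (Days 1, 8, 15, 42, 365) | no | no |
| Synopsis account of follow-up after Day 42 | Day 365 only | Day 365 only |

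Section 9.7 adds only monthly MADRS-S and EQ-5D.

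**Step 3. How much is lost if Table 1 is followed?**

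- MADRS endpoint: Days 15, 42, 180 and 365 planned; 15, 42 and 365 remain. One of four is empty.
- CGI endpoint: Days 8, 42, 180 and 365 planned; 8, 42 and 365 remain. One of four is empty.

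The MMRM for these endpoints (SAP section 5.5) would give no Day 180 estimate. It can still estimate the other visits.

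**Step 4. Are tasks run at MRI1?**

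- Against: section 15 says so directly. Table 1 gives 60 minutes for MRI1 and 90 for MRI2, matching the 1 hour and 1.5 hours in section 15. The synopsis outcome list places the fMRI activation paradigms after dosing.
- For: section 8.5.2 includes tasks at MRI1, and section 9.4.1 implies identical sessions. Yet section 8.5.2 itself allots about 1 hour, which is the no-task duration in section 15.

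Pre-dose task sessions number 0 under section 15 and 1 under section 8.5.2. With 0, a within-person change has no first term, and only a comparison of groups after dosing is possible. Resting-state fMRI is in both sessions, so its change can be computed either way.

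**The case against.** The strongest reply is that these are drafting conflicts rather than missing data. Section 5.5.1 does plan a Day 180 MADRS and allows a video interview when a face-to-face one is not possible, so the absence of a site visit does not rule out a rating. Section 5.5.4 says that CGI shares the MADRS time points, which could be read as bringing Day 180 in. Section 8.5.2 does plan tasks at MRI1. This stands. A reader might infer that the Day 180 and task-change endpoints can never be computed, but the documents do not support that. They support a contradiction whose outcome depends on which section is followed.

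The reply is also right about scale. The endpoints concerned are secondary or exploratory. The synopsis keeps exploratory results out of the Clinical Study Report, and add-on antidepressant treatment is possible from Day 43.

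Two further inferences should be resisted:

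- **The mean over Days 8 to 365.** A reader might blame its uneven weighting on the missing Day 180 rating. Without Day 180, three of four rater MADRS values fall by Day 42; with it, three of five still do. The weighting comes from the visit spacing, and nothing in the plan requires the rater and self-rated means to be weighted alike.
- **AUDIT and DUDIT.** A reader might take section 17.9.1 to promise a before-and-after comparison of these questionnaires, which are given only at web screening. The section speaks of comparing behaviours and also cites urine drug screens, which Table 1 schedules at PET1 and PET2. That comparison has a data source.

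The reply does not remove the conflict with Table 1. Physician or nurse contacts during follow-up have no fixed frequency and no rater scales assigned to them, so they do not fill the gap.

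**Conclusion.** The concern holds as an internal contradiction that should be fixed. Under Table 1, Day 180 rater MADRS and CGI have no scheduled assessment, and one of four time points in each of two secondary endpoints would be empty in both arms. The case is firmer for CGI, where both the schedule and the scale section's own day list omit Day 180, than for MADRS, where section 5.5.1 lists it. For task fMRI, most of the detail favours section 15. If it governs, the exploratory task endpoints cannot be changes from baseline.

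This rests on sites working from Table 1, as sections 8 and 9 direct, and on section 15 describing the intended scanning. The Day 8 primary endpoint, the remaining MADRS and CGI time points, and resting-state change are untouched.

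**What to change.** **Day 180: choose one.**

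- Keep it: add a Day 180 column with a window to Table 1, with rater MADRS, CGI-S and CGI-I; add Day 180 to the CGI days in section 5.5.4 and to the synopsis visit list. On Table 1's own durations this takes 10 + 1 + 1 = 12 minutes per patient, or 30 × 12 = 360 minutes (6 hours) for 30 patients. The video provision in section 5.5.1 could be extended to this contact.
- Drop it: delete Day 180 from the synopsis, section 5.1.2, section 5.5.1 and SAP section 3.2. This costs wording only.

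**Task fMRI.** Make sections 8.5.2, 9.4.1 and 15 state the same content for MRI1 and MRI2. If section 15 governs, reword the task endpoints in section 5.3 and SAP section 3.3 as between-group differences at MRI2 after dosing. This too is wording only. If tasks are wanted at MRI1, correct section 15 and the 60-minute MRI1 entry in Table 1; the present difference between sessions is 90 − 60 = 30 minutes per patient.

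The choice is best made before patients reach the time points concerned, because neither measurement can be obtained afterwards.

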## 5.2 Secondary objective and endpoint

The secondary objective of this study is to evaluate the efficacy of a single 25 mg dose of psilocybin for MDD compared to an active placebo in medically-healthy participants ages 20 to 65, to increase synaptic density in hippocampus and prefrontal cortex. measured as between-group differences in change in [C]UCB-J binding ratio from Baseline to day 15 post dose.

### 5.2.1 Secondary endpoints

- Relative increase (ratio) in [C]UCB-J binding from Baseline to Day 15 post dose

## 5.3 Exploratory Objectives and endpoints

The exploratory objectives of this study are to evaluate the efficacy of a single 25 mg dose of psilocybin for MDD compared to an active placebo in medically-healthy participants ages 20 to 65, measured as between-group differences in:

- Change in p11 concentration in PBMC subsets from Baseline to day 15 Post dose
- Change in BDNF and VEGF concentration in plasma from Baseline to day 15 Post dose
- Change in kynurenic acid in CSF from Baseline to day 15 Post dose
- Change in monoamine and monoamine metabolites in CSF from Baseline to day 15 Post dose
- Change in cytokine concentration (exact markers to be determined based on current literature at time of analysis) in CSF from Baseline to day 15 Post dose
- Change in metrics of whole-brain connectomics and hub characteristics of medial and ventrolateral prefrontal cortex as well as orbitofrontal cortex in the psilocybin treated group as compared to the placebo group, and in relation to clinical outcome (MADRS) as well as PET-outcome (resting state fMRI).
- Change in influence of top-down priors in an instructed fear learning paradigm and its relation to a change in activity of the ventromedial prefrontal cortex and lateral orbitofrontal cortex in the psilocybin treated group as compared to the placebo group, and in relation to clinical outcome (MADRS) as well as PET-outcome (tasked based fMRI).
- Change in Emotion detection under perceptual uncertainty and perspective-shifting ability in relation to large-scale network activity patterns in the psilocybin treated group as compared to the placebo group, and in relation to clinical outcome (MADRS) as well as PET-outcome.
- Change in anxiety symptoms from Baseline to post-dose Day 8, 15, 42 and 365
- Change in functional disability to post-dose Day 8, 15, 42 and 365
- Change in health-related meaning of life and satisfaction with life from Baseline to post-dose Day 8, 15, 42 and 365
- Change in psychological flexibility from Baseline to post-dose Day 8, 15, 42 and 365
- Correlations between biomarkers and scales

